### Ethical considerations

All ethical considerations of this trial were discussed and approved in institutional review board of Shiraz University of Medical Sciences (IR.SUMS.REC.1399.406). Taking informed consent in the acute setting is an important ethical issue with this type of trial. To deal with this issue, we will obtain the consent forms when the patients are in a stable clinical condition and had sufficient time to recover from sedation or analgesics. Using the patients’ umbilical cord Wharton’s jelly tissue-derived MSCs will have the risk of an allergic reaction near zero. Furthermore, using a low balloon inflation pressure and a divided infusion time prevented intracoronary cell infusion complications.

## Discussion

Currently, all the therapeutic measures after AMI are focused to prevent remodeling and further myocyte loss [5]. Regenerative medicine and cell therapy have provided new hopes to not only prevent the remodeling process but also reversing the process by providing new functional cells and increasing the cardiac function capacity [25].

The results from preliminary studies were not very encouraging, and the potential of stem cells for cardiac regeneration became doubted [9]. However, further meta-analyses showed that in certain populations this therapy may be effective. In a meta-analysis from the Cochrane database, it was shown that treatment of young AMI patients with a reduced LVEF with BM-MNCs not only is effective in increasing LVEF but also may have survival and functional benefits [24].

Studies of MSCs have shown greater promise in the field as compared to BM-MNCs. In the TAC-HFT trial, it was shown that MSC are about twice as much effective as the bone marrow-derived mononuclear cells (BM-MNCs) [21]. Meta-analysis of MSC trials showed similar results and depicted a improving LVEF by 3.84% [26] as compared to 2.72% effect seen by BM-MNCs [24].

There is still debate regarding the mechanism by which stem cells, particularly MSCs, impose their therapeutic effects. Current paradigm suggests the paracrine effect theory indicating that most of the beneficial effects after cell therapy are obtained through signals such as cytokines that are released in a paracrine signaling by the injected cells and alter the nearby cells and the recipient heart [29].

Our trial by including the selected patients who are young and have developed with a reduced LVEF after AMI provides important insights in the field in two ways. First, it will show us whether the findings from meta-analysis that indicated cell therapy effect is confined to special population of patients post AMI are reproducible in a clinical trial or not. Second, by performing the second dose injection, it provides us with clues regarding the mechanisms of how MSC may help in the regeneration of cardiac tissue.

## Dissemination

The study will adhere to the principles outlined in the *Declaration of Helsinki*. Data monitoring will be finished by November 2021. Primary and secondary analysis will be initiated after data collection is completed. The results will be ready for submission in December 2021. The manuscript of the trial will be submitted due to the CONSORT statement. According to recommendations, this trial has been registered with a public registry IRCT.ir.

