### Sample size determination

According to the objectives and type of the study and citing previous studies in this field, taking into account the 5% error, 90% power, 3% difference between placebo group and single dose injection group, and another 3% difference between single and double injection groups after the 6 month follow-up period and 1.3 standard deviation and 1:1:1 ratio, the sample size will be estimated in each group using the formula $$ n=\frac{2{s}^2{\left({z}_{1-\raisebox{1ex}{$\alpha $}\!\left/ \!\raisebox{-1ex}{$2$}\right.}+{z}_{1-\beta}\right)}^2}{{\left(\partial \right)}^2} $$ . Due to the length of the study and repeated measurements, using the formula $$ {n}^{\prime }=n\times \frac{1}{1-p} $$, and a drop of 15%, the sample size is decided 16 in each group. Finally, considering that in this study, three groups will be compared and according to the formula, $$ {n}^{\prime }=n\times \sqrt{k} $$, 20 subjects will be needed in each group, so a total of 60 patients will be selected. In the above formula, the values of *z* are constant and equal to 97.5th percentile and 80th percentile of the standard distribution. The ratio of people in the two groups and the effect size are the value divided by the standard deviation.

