### Study participants

Sixty patients will be enrolled in this trial; they should have been hospitalized due to anterior ST elevation myocardial infarction (STEMI), undergone successful primary percutaneous coronary intervention (PCI), and had a LVEF < 40%. Centers participating in the trial are the Alzahra Heart Hospital (Shiraz, Iran), Nemazee Hospital (Shiraz, Iran), and Shahid Faghihi Hospital (Shiraz, Iran). Inclusion and exclusion criteria are listed below:

Inclusion criteria:
Ages 20–60 yearsGenders: BothFirst MI within 3 to 7 daysPost-AMI LVEF less than 40% as assessed by echocardiographyNegative pregnancy test (in women with childbearing potential)Written informed consent

Exclusion criteria:
History of prior anterior myocardial infarctionPatients with regional wall motion abnormalities in the non-infarct regionPrior coronary artery bypass graft (CABG) surgeryPatients with significant valve disease, defined as stenosis or regurgitation graded as greater than moderate (2+)Patients with another etiology of LV dysfunction (known/suspected non ischemic cardiomyopathy, previous anthracycline therapy, known ethanol abuse (greater than 6 oz. ethanol/day on a regular basis)Poor echocardiography windowActive infection or history of recurrent infection or positive test for syphilis (RPR), hepatitis B and C (HBsAg, Anti-HCV), HIV, and HTLV-1Documental terminal illness or malignancyPrevious bone marrow transplantAutoimmune disease (e.g., lupus, multiple sclerosis)

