### Patient follow-up and study endpoints

During the hospital course, patients will be visited every day by a cardiologist. Performed physical examinations and vital signs will be recorded. We will monitor the patients during admission and any signs of arrhythmia, pulmonary emboli, and coronary artery injury will be evaluated and recorded. Blood samples are drawn for measurement of fasting blood sugar (FBS), complete cell blood count (CBC), urea and electrolytes, liver function tests (LFTs), creatine kinase, and cardiac troponin T- and C-reactive protein. An electrocardiogram (ECG) test is also taken. Before the first cell infusion, cardiac magnetic resonance (CMR) imaging and echocardiography will be done. After cell infusion, patients will be discharged from the hospital with a prescription for beta-blocker, angiotensin-converting enzyme (ACE) inhibitor, aldosterone antagonist, aspirin, ticagrelor, statin, and nitrate spray or tablets to take as required and cardiac rehabilitation program. Blood tests, an ECG, and physical exams are again done at the 10th day (at time of admission for second cell infusion), 3-month, and 6-month visits. At the last visit, echocardiography and CMR will be re-performed. All the tests will be recorded.

The improvement in LVEF after 6 months will be the primary efficacy endpoint for this study. Secondary endpoints will be the infarct size of the infarcted and salvaged myocardium at 6 months as assessed by CMR, changes in LV function, left ventricular mass (LVM) index, left ventricular end diastolic volume (LVEDV), left ventricular end systolic volume (LVESD), and global longitudinal strain (GLS) at 6 months as determined by echocardiography.

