### Statistical analysis

All data will remain anonymous before the analysis, which will be done by an independent, expert member of the department not involved in the trial. Based on the findings from previous meta-analysis, a 3% improvement in ejection fraction, as measured by CMR after 6 months, will be considered significant [26]. An intention-to-treat analysis will be performed. We will also analyze the baseline demographic and clinical characteristics for each arm of the study. Mean and standard deviation will be used for continuous variables, and categorical data will be shown by frequencies and percentages. One-way analysis of variance (ANOVA) will be used to perform comparisons of LVEF changes after 6 month (primary endpoint) and also other outcomes between the treatment arms regarding the followed by post hoc Tukey’s test for comparisons of the double-doses-infusion arm with single-dose-infusion group and placebo control-treated groups individually. Only cases with complete follow-up will enter the final analysis. Paired *t*-test will be performed for within-group comparisons. Estimated treatment effect will be reported with 95% CI. All *p* values will be two-sided. Safety events such as the incidence of MACE (death, recurrent AMI, ICD insertion, non-target vessel revascularization…) and serious adverse events (SAE) will be compared among the three arms, and Kaplan-Meier curves will be used to show the pattern of events during the 6-month follow-up. Using Cox’s proportional hazards model, statistical significance and 95% CIs will be reported.

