## Trial status

This trial is still recruiting the patients. Recruitment started on January 2021, and enrollment is estimated to end by November 2021. This protocol is version 2 approved on October 2020. The COVID-19 pandemics did not influence the patient enrollment in this trial.

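### The stated calendar (enrolment to November 2021, monitoring finished in November, results in December 2021) cannot accommodate a 6-month primary endpoint

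*Protocol article*

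**What the plan says.** The relevant statements are in four sections of the protocol article.

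- **Trial status:** "Recruitment started on January 2021, and enrollment is estimated to end by November 2021". The same section says that recruitment is still open.
- **Dissemination:** "Data monitoring will be finished by November 2021"; "Primary and secondary analysis will be initiated after data collection is completed"; and "The results will be ready for submission in December 2021".
- **Patient follow-up and study endpoints:** "The improvement in LVEF after 6 months will be the primary efficacy endpoint for this study". CMR and echocardiography are repeated at the last visit, which is the 6-month visit.
- **Statistical analysis:** "Only cases with complete follow-up will enter the final analysis". The same section also announces an intention-to-treat analysis.

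The planned size is 60 patients, 20 per arm. Sample size determination allows for 15% dropout. The article describes no interim efficacy analysis, staged report or shortened follow-up that would explain the dates.

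**The concern.** Enrolment is expected to end in the same month in which monitoring is to finish, and the results are due one month later. That leaves no room for the 6 months each patient needs before the primary endpoint can be measured. The rule that analysis follows completed data collection does not fit a December 2021 submission if patients are still entering in the autumn of 2021.

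Two things are at stake. If the dates were followed, the complete-follow-up rule would remove later enrollees because of the calendar and not because of anything that happened to them, and the primary analysis would rest on early enrollees only. Monitoring would also end while many patients were still inside their 6-month follow-up.

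**Working it through.** **Step 1. The dates alone, with no accrual assumption.**

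Last 6-month visit = end of enrolment + 6 months = November 2021 + 6 months = May 2022.

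The article's own completion dates are November 2021 (monitoring) and December 2021 (results), so they are not reproduced. The shortfall is about 6 months against the November date and about 5 against December. Working backwards, the last enrolment date that still allows a 6-month visit is:

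- cut-off 1 to 30 November 2021: 1 to 30 or 31 May 2021, depending on how 6 months are counted;
- cut-off 31 December 2021: 30 June 2021.

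**Step 2. How many patients this would affect.**

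This needs an accrual pattern, and the article gives none. Assume even accrual:

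patients with the endpoint = 60 × (last usable enrolment date − recruitment start) / (enrolment end − recruitment start).

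The article gives months and no days, so the start is taken as 1 or 31 January and the enrolment end as 1 or 30 November.

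| Start | Enrolment end | Cut-off | Days ratio | Patients of 60 with endpoint |
|---|---|---|---|---|
| 31 Jan | 30 Nov | 1 Nov | 90/303 | 18 (lowest, November) |
| 1 Jan | 30 Nov | 1 Nov | 120/333 | 22 |
| 1 Jan | 30 Nov | 30 Nov | 150/333 | 27 |
| 1 Jan | 1 Nov | 30 Nov | 150/304 | 30 (highest, November) |
| 31 Jan | 30 Nov | 31 Dec | 150/303 | 30 (lowest, December) |
| 1 Jan | 1 Nov | 31 Dec | 180/304 | 36 (highest, December) |

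The ranges are therefore 18 to 30 of 60 at a November cut-off and 30 to 36 at 31 December. As shares without the endpoint, these are 50% to 70% and 40% to 50%. The planned 15% dropout would leave 60 × 0.85 = 51 patients, or 17 per arm.

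**Step 3. What this would do to power.**

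The calculation is for one pairwise comparison with a 3-point difference, a Tukey critical value for three arms at 5%, and a noncentral t distribution with 3n − 3 degrees of freedom. It compares 17 per arm (planned, after dropout) with 9 per arm (27 of 60). The only SD in the article is 1.3; the others are assumptions to show the range.

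| SD | Power, 17 per arm | Power, 9 per arm |
|---|---|---|
| 1.3 (stated) | above 99% | about 99% |
| 2.0 (assumed) | 97% | 75% |
| 2.5 (assumed) | 86% | 53% |
| 3.0 (assumed) | 69% | 37% |

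At the stated SD, even 6 per arm (18 of 60) gives about 90%. At larger SDs the loss is considerable.

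**The case against.** The strongest reply is that the plan does not authorise a truncated analysis. Dissemination itself puts analysis after data collection, and the 6-month imaging is part of the schedule, so the likely result of optimistic dates is a late paper. This largely stands. A reader might infer that the calendar amounts to an unplanned early look at efficacy. The article does not support that: it describes no such look, and its own sequencing rule points the other way. The rule does not remove the conflict, though, because it is one of the statements that cannot hold together with enrolment to November and results in December.

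Other points on that side:

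- **Wording.** The article ends data monitoring in November 2021; it does not say that data collection closes then. A reader might infer a November closure, but no closing date is given. The conflict does not need one: completed collection must precede analysis, and analysis must precede a December submission.
- **Accrual.** A reader might infer that about half the patients must lack the endpoint. That depends on even accrual. The November end date is an estimate and an upper bound, and faster early recruitment would reduce the loss. Patients enrolled after June 2021 would still lack the endpoint.
- **Power.** A reader might infer that the trial would be underpowered. On the stated SD of 1.3 it would not fall below the planned 90%. Whether 1.3 is credible is a separate question.
- **A slip.** Enrolment may have been written where the end of follow-up was meant, which would make the dates fit. The text does not say so, and the Trial status section would then need correcting.
- **Location.** These are forecasts in closing sections, outside the design and analysis sections. That makes the correction easy, but the dates remain incompatible.

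**Conclusion.** The point holds as an internal contradiction. With a 6-month primary endpoint, enrolment until November 2021 puts the last primary measurement in May 2022, about 6 months after the stated end of monitoring and 5 months after the stated date for results. This rests on the article's text alone.

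The consequence is conditional: only if the dates were kept would patients enrolled after about May or June 2021 be lost from the primary analysis. The size of that loss, 30 to 42 patients at a November cut-off or 24 to 30 at 31 December, rests on even accrual. It compares with 9 lost under the planned 15% dropout. No single power figure can be claimed. The dates are wrong as written and should be corrected.

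**What to change.** Reconcile the Dissemination and Trial status sections in one of two ways:

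- if enrolment does run to November 2021, move the end of data monitoring, the database lock and the submission date past the last patient's 6-month visit, that is, past May 2022; or
- if the enrolment date is the slip, correct it. To keep a November 2021 close, the last patient would have to be enrolled by May 2021.

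In either case, add a sentence saying that the between-arm efficacy analysis is run only after every randomised patient has passed the 6-month window. That makes the existing sequencing rule explicit and prevents the complete-follow-up rule from being applied to patients whose visit is not yet due.

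Under the first option the cost is a change of wording and a reporting date about 6 months later. No extra patients or measurements are needed.

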## Trial status

This trial is still recruiting the patients. Recruitment started on January 2021, and enrollment is estimated to end by November 2021. This protocol is version 2 approved on October 2020. The COVID-19 pandemics did not influence the patient enrollment in this trial.

## Data Availability

After publication of the final results, the data will be available based on the requests.

## Abbreviations

MCSs: Mesenchymal stromal cell
LVEF: Left ventricular ejection fraction
AMI: Acute myocardial infarction
WJ-MSCs: Wharton’s jelly mesenchymal stromal cell
MI: Myocardial infarction
BM: Bone marrow
HF: Heart failure
BM-MNCs: Bone marrow-derived mononuclear cells
EF: Ejection fraction
CMR: Cardiac magnetic resonance
GLS: Global longitudinal strain
DE: Delayed enhancement
MACE: Major adverse cardiac events
SAE: Serious adverse events
DSMB: Data and Safety and Monitoring Board
